**Fig. 3 Fig3:**
[figure not shown]
COVID-HEART study CMR protocol. The full protocol takes approximately an hour, and comprises (in order of acquisition): localisers and axial HASTE stack, cine images of the left ventricle in long-axis views, pre-contrast T1 mapping and T2 mapping, rest myocardial perfusion after injection of 0.05 mmol/kg of gadolinium based contrast agent (GBCA) followed immediately with 0.1 mmol/kg top-up (giving a total dose of 0.15 mmol/kg). Then a ventricular short-axis stack and aortic cine images (aortic distensibility, followed by late gadolinium enhancement (LGE) imaging and post-contrast T1 mapping. The last component (dependent on patient suitability) is stress perfusion imaging, performed after administration of adenosine stress at dose of 140-210mcg/kg/min, utilising a further 0.05 mmol/kg of GBCA

3)* Functional assessment by 6-min walk test.* Participants will asked to perform a standard 6MWT at the 6-month visit following the American Thoracic Society guidelines [35]. Patients will be instructed to walk along a corridor and turn at 15 m in order to cover the maximum distance in 6 min under the supervision of study investigators. The investigators will tell the participant how much time had elapsed every 2 min and encourage participants to continue at intervals of between 30 s and 1 min. At the end of 6 min, participants will be asked to stop, and the distance walked will be measured in metres.

4)* Quality of life questionnaires.* All participants will be asked to complete patient-reported health status questionnaires (36-Item Short Form Health Survey; SF-36v2) and a health-related QoL questionnaire (EQ-5D-5L) at baseline and 6 months. These will be performed either face to face, by telephone or by post, depending on local site and individual patient circumstances and preferences. These questionnaires were chosen to align with other UK national COVID-19 research studies (e.g. C-MORE/P-HOSP-COVID).

5)* Laboratory investigations*. As part of clinical routine, patients will undergo routine laboratory testing, including full blood count, renal and liver profile, inflammatory markers, and cardiovascular biomarkers (e.g. troponin and brain natriuretic peptide (BNP)). Additional research blood sampling for genetic analysis/inflammatory markers will be performed, if not already acquired from participation in other UK COVID-19 research studies. 10 ml of blood will be drawn into an ethylenediaminetetraacetic acid (EDTA) bottle. The tube will be inverted 5 times and transferred on ice. The sample will be centrifuged for 20 min at 2000G at 4 °C. The sample will be divided into 6 × 1 ml Thermo Matrix tubes. Subsequently a pipette will be used to provide 5 aliquots. Plasma will be taken from the centre of each sample avoiding the buffy coat layer, which will be retained separately. Samples will be labelled with a unique study ID and stored locally on-site, pending batch transfer for analysis at Leicester University and the University of Glasgow.

### Follow-up

Patients will be followed up at 6 months (± 4 weeks) from date of the diagnosis of COVID-19, and invited to have a second CMR scan, ECG, QoL assessment (SF-36v2 and EQ-5D-5L) and functional assessment (6MWT). In addition, routine clinical outcome data will be collated up to 5 years post-infection from: electronic patient records, general practice information systems, National Institute for Cardiovascular Outcomes Research (NICOR) and NHS Digital (eDRIS in Scotland).

### Study outcomes

#### Main outcomes

Presence, extent, distribution of LGECMR biventricular volumes and functionFunctional capacity (6MWT) and QoL measuresLong-term clinical outcomes

#### Exploratory outcomes

CMR: T1, T2 mapping indices, myocardial strain, myocardial perfusion, aortic distensibility measures.ECG indicesBiomarker and genetic analysesCoronary atheroma extent (coronary vascular sub-study)

### Analysis plan

The prevalence and extent of cardiac involvement in patients with COVID-19 and raised troponin will be described by CMR. Predictors of cardiac dysfunction and recovery such as: blood biomarkers, the severity of the acute infection, genetics, and comorbidities will be identified. The determinants of adverse clinical outcome in this population will also be examined. Outcome assessments (clinical event adjudication) will be undertaken at individual hospital sites according a pre-specified standard definition set (Appendix 1) contained with a signed clinical outcome charter.

1)* CMR data:* All quantitative analyses will be performed blinded to participant status. CMR data sets will be analysed by a disseminated core-lab technique as previously used in the BSCMR UK valve consortium [36]. LV structure and function including mass and wall thickness will be analyzed using a clinically validated artificial intelligence (AI) analysis platform [37]. Left atrial area and global longitudinal shortening will be similarly analyzed by further validated artificial intelligence approaches [38]. LGE patterns will also be classified into patterns reflecting likely aetiology and quantitative assessment will be performed by semi-automated signal intensity analysis according to the full width at half maximum technique and other thresholds where appropriate [36]. Evidence of pericarditis will be assessed on cine, LGE and tissue characterisation images. T1 and T2 mapping will be quality-assured and analysed to establish the global and segmental T1 and T2 values, using standardised approaches developed by the Oxford group [39, 40]. Myocardial perfusion assessment for the coronary vascular sub-study will be carried out by segmental and global quantitative myocardial blood flow calculation during rest and adenosine stress; it will be calculated from fully automated in-line quantification [41, 42]. In addition, visual perfusion defects will be scored semi-quantitatively by 2 observers as previously described [43] with disagreement resolved by a third reader. The likelihood of microvascular disease (patchy perfusion defects not following the distribution of a coronary distribution or circumferential defects not affecting apical segments) will be recorded. Circumferential strain and strain rates will be generated by automated tissue tracking software (cvi42, Circle Cardiovascular Imaging, Alberta, Calgary, Canada) as previously described [44]. Aortic distensibility will be assessed using blood pressure assessments and measurements of the cross-sectional area of the ascending aorta in systole and diastole on axial cine slices at the level of the right pulmonary artery. Distensibility = (aortic max lumen area − aortic min lumen area)/(aortic min lumen area * [systolic blood pressure − diastolic blood pressure]).

2)* ECG data:* The standard and digital 12-lead ECGs will be electronically transferred via the study portal into the image repository at the coordinating centre in Glasgow, Scotland. Digital ECGs will be analysed in the University of Glasgow ECG core lab utilising the previously validated Glasgow ECG analysis software [45]. A full set of measurements plus interpretation will be extracted for analysis of ECG changes and statistical processing, with the aim of determining sensitive and specific criteria for diagnosing myocarditis from the ECG, and prognostic ECG findings in this population [46]. ECGs available in printed form will also be electronically transmitted in pdf format to the ECG Core Lab for standardised review based on the same criteria as used in the Glasgow program. Manually classified changes will also be subject to statistical analysis.

3)* Laboratory data:* All blood samples will be transferred to the central coordinating centre in Leicester, England and analysed in the University of Leicester Cardiovascular Research Centre and the BHF Glasgow Cardiovascular Research Centre, University of Glasgow. Analysis will entail novel cardiovascular biomarkers (e.g. vascular cell adhesion molecule, interleukin-6) and markers of genetic susceptibility to COVID-19. The genetic analysis will be used to explore links specifically in the black and minority ethnic populations and linked in with existing cohorts for genotyping (The Genetics and Vascular Health Check study, The Biomedical Research Informatics Centre for Cardiovascular Science and UK Biobank).

4)* 6MWT:* As per the American Thoracic Society guidelines, the distance walked (measured in meters) in 6 min will be recorded by the investigator supervising the test. Symptoms of perceived breathlessness will be recorded on the Borg scale and if the test was stopped early, the reason will be recorded.

5)* Quality of life questionnaires:* Patients’ responses to the 36-Item Short Form Health Survey and the health-related QoL questionnaire (EQ-5D-5L) will be recorded in the eCRF by the investigators. Each of the 8 health domains measured by the SF-36v2 will be given a combined percentage score, with higher percentage scores representing a better level of functioning. Each of the 5 domains of the EQ-5D-5L will be scored on a 1–5 scale, with level 1 indicating no problems with a particular domain and level 5 indicating extreme problems. Health state of an individual patient will be determined by combining the levels from all the domains.

### Statistical considerations

#### Sample size considerations

Patients in work package-1 will originate from the open national image repository for all UK CMR centres, and therefore no sample size calculation is required. For work package-2, based on the assumption that the mean prevalence of myocardial involvement was 12% (mid-range) from previous studies, a precision of 3.5% and 95% confidence level, a sample size of 333 ± 3.5% would be required. To account for a 10% drop out rate, it was calculated that 370 patients are needed.

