Multiple studies have demonstrated that myocardial injury, characterised by elevation in serum cardiac biomarkers, is common in COVID-19. The prevalence of myocardial injury, however, is variably reported, with early studies quoting a prevalence of 8–12% in hospitalised patients, whilst more recent data suggest that it is possibly much higher [4, 7]. Subsequently, a larger multicentre study of 305 patients identified an elevated troponin in more than half of the hospitalised patients [8]. A recent German cohort study reported imaging evidence of myocardial injury defined by cardiovascular magnetic resonance (CMR) in over 70%, although whether this was pre-existing or consequence was unclear with single time-point imaging [9]. The underlying mechanism of cardiac injury and troponin elevation remains unclear, but there are several potential explanations. Troponin T release is commonly seen in critically ill patients because of oxygen supply–demand mismatch and cytokine release, acute heart failure, RV strain (secondary to pneumonia, hypoxia and increased pulmonary artery pressure) and acute arrhythmia [10–12]. Furthermore, the acute-phase response to severe coronavirus infection can lead to coagulopathy and microvascular thrombosis, for example in the pulmonary and coronary circulations [13, 14]. Pre-existing coronary risk factors, such as hypertension and diabetes also predispose patients with COVID-19 to myocardial infarction in the acute setting, possibly implicating it as another potential disease mechanism [15]. On a cellular level, however, direct myocardial injury may occur due to viral angiotensin-converting enzyme-2 transmembrane receptor mediated damage, microvascular dysfunction or increased vessel wall permeability [16].

Troponin elevation in hospitalised COVID-19 patients is associated with higher morbidity and increased short-term mortality [4, 8, 17–21], particularly in those who also have underlying CVD [16]. Those with CV comorbidities (diabetes, hypertension, heart failure or CAD/peripheral artery disease) are heavily over-represented in both severe COVID-19 and mortality [22, 23].

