### Study population

Inclusion criteria include—hospitalised-recovering patient population (age ≥ 18 years), or those recently discharged from hospital, with a diagnosis of COVID-19 based upon either a pathology or radiology diagnosis, with cardiac biomarkers (troponin I or T) increased above the sex-specific upper reference limit of the local laboratory range. Exclusion criteria include being unable or unwilling to consent, contraindication to CMR, pregnancy or breast-feeding.

Contemporary patient cohorts acting as control data will be acquired for comparative CMR analysis. These will be derived from ethically approved local research studies from the recruiting centres for COVID-HEART using the same CMR scanners (vendor and field strength). As the patients in COVID-HEART are COVID( +) and Troponin( +), control populations will include:A population matched for age and CVD risk factors, who have been hospitalised and are COVID( +) and Troponin(−) [e.g. Capturing MultiORgan Effects of COVID-19 (C-MORE) cohort, Oxford, UK; NCT04510025].A population matched for age and CVD risk factors, who have tested COVID(−) and Troponin(−).

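### The ±3.5-point precision behind 333/370 patients rests on a 12% prevalence that is not justified for a CMR endpoint in an all troponin-positive cohort

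*Protocol article*

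**What the plan says.** The Sample size considerations section plans work package-2 on one proportion. It takes "the mean prevalence of myocardial involvement was 12% (mid-range) from previous studies, a precision of 3.5% and 95% confidence level", and concludes that "a sample size of 333 ± 3.5% would be required". It then adds: "To account for a 10% drop out rate, it was calculated that 370 patients are needed". No citation or range accompanies the 12%.

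The Background is the only other place where 12% appears as a prevalence. It reports "early studies quoting a prevalence of 8–12% in hospitalised patients", straight after describing myocardial injury in terms of raised serum biomarkers. It adds that newer data suggest the figure may be much higher. It cites a 305-patient study with raised troponin in more than half of inpatients, and a German cohort with "imaging evidence of myocardial injury defined by cardiovascular magnetic resonance (CMR) in over 70" per cent. It also expects structural abnormalities to be likely when troponin is raised, and cites a CMR diagnosis in up to 90% of patients with raised troponin and non-obstructive coronary arteries.

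Under Study population, patients qualify "with cardiac biomarkers (troponin I or T) increased above the sex-specific upper reference limit of the local laboratory range". Under Objectives and Statistical analysis, the first primary objective is to characterise myocardial involvement in these patients, with prevalence estimates and 95% confidence intervals.

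**The concern.** A confidence interval for a proportion is narrow when the proportion is near 0 or 1 and widest at one half. A planning value of 12% therefore gives a favourable precision, and that precision carries over only if the true prevalence is about as extreme.

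Two things cast doubt on 12% here. First, the only figure in the article that it matches describes how often biomarkers are raised among inpatients. In work package-2 every patient has a raised troponin by design, so that quantity is already fixed by the entry criterion. What remains to be estimated is a different measure (CMR) in a different population (troponin-positive patients). Second, the article's own account of that population points well above 12%.

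This is the only precision target in the article, it serves a primary objective, and it is the sole stated reason for recruiting 370 patients. A reader would expect an interval of ±3.5 points that the design may well not give.

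**Working it through.** **Inputs.** From Sample size considerations: prevalence p = 0.12, half-width d = 0.035, 95% confidence (z = 1.96), 333 evaluable, 10% dropout, 370 enrolled. From the Background: 8–12% (biomarkers, inpatients), over 70% (CMR), up to 90% (CMR diagnosis, raised troponin with non-obstructive coronaries). The other prevalences below are assumptions chosen to show the range.

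**Step 1: reproduce the stated figures.** n = z²·p(1−p)/d² = 1.96² × 0.12 × 0.88 / 0.035² = 331.2, rounded up to 332. The article states 333, a difference of one patient. For dropout, 333/(1 − 0.10) = 370, exactly as stated. The half-width at 333 is 1.96 × √(0.12 × 0.88/333) = 3.49 points. The calculation is sound given its input.

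**Step 2: the mid-range label.** If the 8–12% range is the source, its midpoint is (8 + 12)/2 = 10%, and 12% is its upper end. At 10% the same formula gives 283 patients. This step depends on an inferred source.

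**Step 3: precision at other prevalences.** Half-width = 1.96 × √(p(1−p)/n), in percentage points. The last column is the number of evaluable patients needed for ±3.5.

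| True prevalence | n = 333 | n = 370 | n for ±3.5 |
|---|---|---|---|
| 12% or 88% | 3.49 | 3.31 | 332 |
| 20% or 80% | 4.30 | 4.08 | 502 |
| 30% or 70% | 4.92 | 4.67 | 659 |
| 50% (worst case) | 5.37 | 5.09 | 784 |
| 90% | 3.22 | 3.06 | 283 |

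**Step 4: where ±3.5 holds with 333.** It requires p(1−p) ≤ 333 × 0.035²/1.96² = 0.1062. Solving p² − p + 0.1062 = 0 gives p = 0.121 and 0.879. The target is met at or below about 12% and at or above about 88%, and missed in between.

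**Step 5: size of the gap.** Relative to 3.5, the interval is 4.92/3.5 = 1.41 times as wide at 70% and 5.37/3.5 = 1.53 times as wide at 50%. In absolute terms the loss is 1.4 to 1.9 points.

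**The case against.** **The source of the 12% is not stated.** The link to the 8–12% range is an inference. Because 12% is not the middle of that range, the authors may have had another range in mind that a condensed article does not show. This stands: the article does not establish that 12% came from unselected inpatients. It does not rescue the figure, because nothing in the article justifies 12% for CMR findings in troponin-positive patients.

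**The precision might still be met.** A reader might infer that ±3.5 fails at every prevalence the Background supports. It does not. The up-to-90% figure concerns patients with raised troponin, and at 90% the half-width is ±3.2. That figure is an upper bound on diagnostic yield in a subgroup, but it is enough to make the shortfall conditional.

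**The alternatives are no better sourced.** A reader might take 50–70% as the correct planning prevalence. The documents do not support that. The more-than-half figure is a troponin rate in inpatients, which is again the entry criterion, and the over-70% cohort is not described as troponin-selected. So 50% serves only as the binomial worst case and 70% as an illustration.

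**The practical loss is small.** Objective 1 can be estimated from the baseline scan, so patients lost before 6 months can still contribute. If all 370 baseline scans are usable, the half-width over 20–80% is ±4.1 to ±5.1. The analysis is descriptive, and no test or decision rule in the article hangs on ±3.5. This stands, and it limits the severity.

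**Conclusion.** The concern holds as a fault in the planning input. The arithmetic is correct, but the 12% is unsourced, is mislabelled if it comes from the 8–12% range, and is not justified for CMR-defined involvement in a cohort selected for raised troponin. The stated ±3.5 points is therefore unsupported. With 333 evaluable patients it is missed for any true prevalence between about 12% and 88%, with a half-width of ±4.3 to ±5.4 over 20–80%.

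This rests on a simple binomial interval and on assumed prevalences, since the article gives no CMR prevalence for troponin-positive COVID-19 patients as a whole.

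A reader might conclude from the last column of the table that the study is too small and needs 659 or 784 evaluable patients. The article does not support that: an interval of about ±5 points is still usable for a descriptive prevalence, and the interval reported from the observed data will be valid whatever was assumed at planning. This is a should-fix, not a must-fix.

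**What to change.** Keep 333 evaluable and 370 enrolled, and rewrite the sample size paragraph:

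- Say that N was derived from a 12% prevalence, give the source of that figure, and acknowledge that it does not describe CMR findings in a troponin-positive cohort. Do not present another prevalence as the one used for planning, because that would misreport how 333/370 arose.
- Replace the single ±3.5-point claim with the 95% half-width for 333 (and for 370, if all baseline scans are usable) over a range of prevalences labelled as assumptions, for example 20–90%, with the worst case of ±5.4 at 50% stated.
- Correct or remove the mid-range label, and attach the ± to the prevalence estimate instead of to the number of patients.

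The cost is one paragraph and a less favourable stated precision. No extra patients are needed and the analysis does not change.

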### Statistical analysis

Statistical analyses will be conducted after production of a signed statistical analysis plan and once baseline and follow-up data collection has been completed. Broadly, the statistical methods for each study objective will be as follows:to characterise the nature and extent of myocardial involvement in COVID-19 patients with an elevated troponin, analyses will be descriptive, and will involve estimation of prevalence with 95% confidence intervals (CIs);to assess how cardiac involvement and clinical outcomes associate with recognised risk factors for mortality in COVID-19 (age, sex, ethnicity and comorbidities) and with genetic factors, we shall present tabular and graphical descriptive summaries within subgroups, and use logistic regression to test for associations and provide estimates with 95% CIs;to evaluate if differences in myocardial recovery at 6 months are associated with demographics, genetics and CV comorbidities (diabetes, hypertension, heart failure and CAD/peripheral vascular disease), descriptive summaries, and linear and logistic regression methods will be applied;to understand the association between recovery status at 6 months and patient-reported QoL and functional capacity, descriptive methods, and linear regression will be used.

To assess whether there are characteristic ECG findings specific for SARS-CoV-2 myocarditis, measures of diagnostic performance will be calculated, and ROC analyses will be used.

In the coronary vascular sub-study, descriptive methods will be used to establish the nature and prevalence of myocardial ischaemia and microvascular dysfunction, and linear regression methods, including mixed effects methods for modelling myocardial blood flow within segments 1–16 of the American Heart Association 17-segment model, will be used to assess risk factors.

Throughout these analyses, levels of missing data will be reported, and regression models will be fitted using multiple imputation of missing predictor variables. Where appropriate, data from other cohorts will be used as control populations.

